**Aim 2. Sleep characteristics and psychiatric symptom profiles**					
2a. Sleep profiles in patients with mental disorders	Patients with mental disorders	Identify latent profiles integrating sleep symptoms.	Clustering features: Sleep measures (e.g., ISI, RU-SATED), External validators: EQ-5D-5L, SWLS	Dimension reduction: Uniform manifold approximation and projection Clustering: Density-Based Spatial Clustering of Applications with Noise, hierarchical clustering, k-means, Gaussian mixture models Group comparisons across profiles: one-way ANOVA with Tukey’s HSD (if assumptions met) or Kruskal–Wallis test with Steel–Dwass post-hoc tests for continuous variables; chi-square tests for categorical variables.	Exploratory
2b. Sleep profiles in patients with diabetes	Type 1 and type 2 diabetes	Identify latent profiles integrating sleep symptoms.	Clustering features: same as 2a External validators: EQ-5D-5L, SWLS	Same as 2a, plus between-group comparisons of profile distributions and validators	Exploratory
2c. Psychiatric profiles in patients with developmental disabilities	Patients with developmental disabilities	Identify latent profiles integrating psychiatric symptoms.	Clustering features: Psychiatric symptoms (e.g., PHQ-9, GAD-7) External validators: EQ-5D-5L, SWLS	Same as 2a	Exploratory

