### 2.6 Sample Size and Sampling

Because this is a registry-based observational study, the study size will primarily be determined by the inclusion of as many feasible participants as possible within prespecified diagnostic strata, consistent with the survey company’s prior recruitment performance. A pragmatic target of 200–300 participants per group will be set, yielding an overall enrollment target of 3000–3300 participants. To contextualize this range, 200–300 participants per stratum corresponds approximately to 95% confidence-interval half-widths of ± 6.9% to ± 5.7% for proportions near 0.50, detectable standardized mean differences of *d *≈ 0.28 to 0.23 for two-group comparisons, and detectable correlations of *r *≈ 0.20 to 0.16. For more complex structural equation modeling and person-centered analyses, adequacy depends strongly on the model complexity, measurement quality, class separation, convergence, and stability; accordingly, these analyses will be interpreted primarily using model fit, convergence, and stability criteria, and disease-specific profiling analyses will be undertaken only if sufficient sample sizes are obtained [34].

Because online surveys tend to disproportionately attract younger respondents, age-stratified quota sampling will be employed to ensure adequate representation across age groups. Minimum quotas will be set at 20 participants per group for each age decade in the 20s (including ages 18 and 19), 30s, 40s, and 50s, and at least 10 participants per group for individuals aged 60 years and older. These quotas will be applied flexibly in groups with limited numbers of registered panel members.

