For Aim 2, latent profiles integrating the sleep characteristics and psychiatric symptoms measures will be derived using uniform manifold approximation and projection embeddings in combination with multiple clustering algorithms. The optimal number of clusters will be determined according to a comprehensive clustering validation framework [91], incorporating multiple internal validation criteria. Differences in the psychological and demographic variables between the clusters will be evaluated using one-way analysis of variance (ANOVA) with Tukey’s Honestly Significant Difference (HSD) post-hoc test when assumptions are met, or the Kruskal–Wallis test with Steel–Dwass post-hoc comparisons otherwise, for continuous variables and chi-square tests for categorical variables.

For Aim 3, the analyses of measurement foundations and attitudes toward digital health technology and AI therapy will include CFA for the eTAP-J, ASSURE-HT, and ASSURE-AI scales as well as regression and ANOVA models to assess group differences. The associations among attitudes toward digital health technology (e.g., acceptance, anthropomorphism, and ethical concerns) and QOL will be examined using serial mediation models.

To assess the robustness of the main findings, prespecified sensitivity analyses will be conducted by varying the model specifications and key assumptions. Specifically, the analyses will be re-estimated using alternative scoring approaches or short-form versions of the questionnaires, varying the thresholds for categorized outcomes, allowing non-linear terms for continuous predictors, and perturbing clustering parameters. The stability of the results will be evaluated across these alternative specifications.

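### The stability check named for the Aim 2 profiles tests sensitivity to analyst settings, not whether the profiles would recur in other patients

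*Protocol article*

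**What the plan says.** Section 2.7 states the purpose: "To assess the robustness of the main findings, prespecified sensitivity analyses will be conducted by varying the model specifications and key assumptions". Of the variations it then lists, the one aimed at clustering is the last, and the yardstick follows it: "allowing non-linear terms for continuous predictors, and perturbing clustering parameters. The stability of the results will be evaluated across these alternative specifications".

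The profiles are to be "derived using uniform manifold approximation and projection embeddings in combination with multiple clustering algorithms". Table 1, row 2a, lists them as "Clustering: Density-Based Spatial Clustering of Applications with Noise, hierarchical clustering, k-means, Gaussian mixture models", and rows 2b and 2c refer back to it. On the number of clusters, section 2.7 says: "The optimal number of clusters will be determined according to a comprehensive clustering validation framework [91], incorporating multiple internal validation criteria".

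Section 2.6, on structural equation models and person-centred methods, says that "these analyses will be interpreted primarily using model fit, convergence, and stability criteria". It does not define the stability criteria. Section 2.7 is the only place in the article that describes a stability evaluation.

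Table 1 types 2a to 2c as exploratory. Section 2.5 asks for caution with exploratory results and for replication in later studies, and refers to the Supplementary Materials (not available here) for the full specifications.

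**The concern.** A clustering algorithm returns groups whether or not discrete groups exist. Two different questions can be asked about the result:

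- Would the same patients be grouped alike under slightly different settings?
- Would a new sample from the same population produce the same groups?

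The check in section 2.7 answers the first. A reader of a profile paper usually takes stability to mean the second. A partition that follows the accidents of one sample can be found again after a small change of settings, because the accidents are still there.

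The other steps named in the article do not fill the gap. The internal validation criteria are computed on the same data. The comparisons on EQ-5D-5L and SWLS would come out positive even if the profiles were only slices of a severity gradient.

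At stake is how 2a to 2c are described. The last paragraph of the Discussion foresees registry profiles informing clinical assessment, policy and resource allocation. Profiles called stable on the strength of this check could be read as reproducible when that was never tested.

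**Working it through.** **The plan's own figures.** The article gives no figure for cluster stability. The section 2.6 figures for 200 and 300 per stratum do reproduce (two-sided 5%; 80% power assumed):

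- half-width 1.96 × √(0.25/n) = 6.93% and 5.66%
- d = 2.80 × √(2/n) = 0.280 and 0.229
- r = tanh(2.80/√(n−3)) = 0.197 and 0.161

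They do not bear on clustering.

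**Sizes.** Section 2.2 lists eight mental-disorder groups (counting insomnia, ADHD and ASD) and two diabetes groups. At 200–300 each, 2a has 8 × 200 to 8 × 300 = 1,600–2,400 patients. 2b and 2c, with two groups each, have 400–600.

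**Index.** The adjusted Rand index (ARI) is (pairs grouped alike − number expected by chance) / (maximum − number expected by chance). It is 1 for identical partitions and about 0 for chance. For split halves, half A's solution is applied to half B and compared with half B's own solution.

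**Simulation 1, k-means.** Assumed: eight scales, one or two continuous factors, loadings 0.55–0.80, no discrete profiles, k = 3–4. The mild change is a new seed, or 4 versus 5 principal components.

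| Data | Same patients, mild change | Split-half |
|---|---|---|
| No profiles, n = 400–600 | 0.90–0.99 | 0.40–0.71 |
| No profiles, n = 2,000 | 0.96–0.99 | 0.50–0.81 |
| Profiles 3.5 SD apart | 1.00 | 0.85–0.95 |

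A repeat gave 0.91–0.98 against 0.46–0.65 at n = 500, and 0.95–0.99 against 0.56–0.82 at n = 2,000. A further k-means run without clusters gave 0.82–0.98 against 0.34–0.79; there, changing k or the algorithm on the same patients gave only 0.39–0.62.

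**Simulation 2, embedding then k-means.** A neighbour-graph spectral embedding stood in for UMAP, with eight scores and k = 3. Values are for n = 250 / n = 1,600.

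| Data | Same patients, 15 vs 20 neighbours | Split-half | Fresh sample |
|---|---|---|---|
| Uncorrelated, no clusters | 0.77 / 0.78 | 0.07 / 0.07 | 0.07 / 0.07 |
| One factor, no clusters | 0.90 / 0.95 | 0.51 / 0.68 | 0.57 / 0.71 |
| Three true clusters | 1.00 / 1.00 | 1.00 / 1.00 | 1.00 / 1.00 |

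Moving the neighbour count from 15 to 10 or 30 gave 0.86–0.92 for one-factor data and 0.56–0.67 for uncorrelated data.

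**Larger changes on the same patients (setting of simulation 2).**

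| Change | No clusters | Three true clusters |
|---|---|---|
| k = 3 vs 4, raw scores | 0.26–0.53 | 0.86 |
| k-means vs Ward, raw scores | 0.12–0.44 | 0.99–1.00 |
| k-means vs Ward, embedded | 0.45–0.73 | 1.00 |
| DBSCAN radius +20%, embedded | 0.36–0.57 | 0.64–0.77 |

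These changes do expose the absence of clusters. But true clusters score 0.64–0.77 under the DBSCAN change, no better than the 0.77–0.95 that cluster-free data score under the 15-to-20 neighbour change. What counts as stable therefore depends on which setting is moved and how far.

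**Limit of split halves.** With raw k-means on one-factor data, split-half ARI was 0.64 at n = 250 and 0.87 at n = 1,600. A pure gradient can recur well in a large sample.

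**External validators.** In cluster-free data with a validator correlated 0.4 (assumed) with the first factor, ANOVA across the k-means groups gave p < 0.001 in every dataset (n = 500 and 2,000; 25 datasets per setting). The validator comparison does not detect the problem.

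**The case against.** - *The article is a condensed document.* The full specifications and the validation framework cited for the number of clusters are not at hand, and either may include resampling. This stands: it cannot be said that the plan as a whole lacks such a check. What can be said is that the check the article does name, and ties to robustness, answers a different question.
- *Sections 2.6 and 2.7 are not explicitly linked.* Correct. Reading the 2.7 evaluation as the stability criterion of 2.6 is an inference, though the article offers no other description.
- *The check can fail.* A reader might infer that it would look stable almost whatever the data. The working contradicts this: changing k, the algorithm or the DBSCAN radius mostly gave low agreement without clusters, and Table 1 plans four algorithms.
- *Aim 2 is exploratory.* A reader might infer that profiles will be presented as established. Table 1 and section 2.5 do not support that. The label limits what may be concluded, but it does not turn a settings check into a test of recurrence.
- *The latent profile analysis in 1d.* A reader might extend the point to it. Table 1 gives 1d its own criteria (BIC, entropy, interpretability) and sensitivity analyses, and no latent profile model was simulated, so the point does not reach 1d.

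**Conclusion.** The point holds for 2a to 2c in a limited form. The named check measures sensitivity to settings and leaves recurrence in other patients untested. With correlated scales and no discrete profiles, mild perturbation gave ARI of about 0.8–0.99 on the same patients, against about 0.3–0.8 for split halves (0.87 at the highest). With uncorrelated scales the figures were 0.56–0.78 and 0.07 under the embedding. Larger perturbations do reveal the problem, but the article does not fix their range.

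These values rest on assumed scale numbers, correlations and k, and on stand-ins for UMAP, so they should be read as ranges. Severity is modest, because the sub-studies are labelled exploratory, replication is required, and the Supplementary Materials may already cover the gap.

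**What to change.** In section 2.7 and Table 1, rows 2a to 2c:

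1. Add repeated split-half or bootstrap agreement of the whole pipeline (embedding, algorithm and choice of k), stratified by diagnosis. Report the ARI and the agreement on k. State how patients in one half are assigned to the other half's profiles, and how DBSCAN noise points are counted.
2. Compare the result with the same index in no-cluster reference data of matching size and correlation, run through the same pipeline. Do not use a fixed cut-off such as 0.80: a single severity gradient reached 0.79–0.87 at about the size of 2a.
3. Keep parameter perturbation as a secondary check, described as sensitivity to settings.
4. If the Supplementary Materials already specify resampling, one sentence in 2.7 naming it as the stability criterion is enough.

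Feasibility: halves would hold about 800–1,200 patients in 2a and 200–300 in 2b and 2c. For the smaller two, the bootstrap may be preferable.

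Cost: wording and computing time, with no new data. The downside is that some profile solutions may have to be reported as not reproducible.

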### 2.8 Data Management and Quality Assurance

Data collection will be conducted through Macromill’s secure online research platform. At the beginning of the survey, participants will be presented with a pledge item asking them to commit to responding carefully, and only those who agree will be allowed to proceed to the subsequent questions [92]. The research team will receive only anonymized survey data from Macromill; no directly identifiable personal information (e.g., names, addresses, e-mail addresses, and contact details) will be provided. According to the company’s publicly available quality management policy, duplicate registrations using the same e-mail address or overlapping personal information are automatically rejected at the system level. Furthermore, during survey administration, the system identifies device cookies to prevent multiple submissions from the same terminal. Consequently, duplicate responses from the same individual are technically prevented. The survey interface requires the completion of all mandatory items and incorporates built-in logic and consistency checks to ensure data integrity. To enhance response quality, the survey platform automatically saves responses upon page transition, allowing participants to pause and resume at any point. To protect data validity, completion within 24-hours of survey initiation is required; surveys not submitted within this window are treated as withdrawal of consent and excluded from analysis.

Files are transferred via institution-approved encrypted channels and stored on access-controlled servers. According to the FAIR principles [21], a prespecified data dictionary governs variable naming conventions, valid ranges, skip patterns, scoring rules, and derivations. Using this specification, the research team generates a de-identified analytic dataset and a versioned codebook with an auditable change log. Following the publication of the primary results, the registry dataset will be released through Zenodo, with a dataset-level DOI assigned at publication. Record metadata will be available in machine-readable formats, including DataCite, DCAT, and JSON-LD using Schema.org vocabulary. A public versioned data dictionary will accompany each release in CSV format, with clearly labeled columns and definitions documented in an accompanying README. Programmatic access will be supported through Zenodo’s REST API and OAI-PMH; no custom API and variable-level persistent identifiers are planned for the initial release. Each release will also include clear licensing, versioning, and provenance documentation to support reuse. Additional details on governance, data derivation and versioning, access control, data retention and disposal, and dataset separation are provided in the **Supplementary Materials**.

### 2.9 Ethics and Dissemination

The study protocol has received ethical approval from the relevant institutional review board (ID R07-137). Digital informed consent will be obtained from all participants before participation. The study findings will be disseminated through peer-reviewed publications, conference presentations, and plain-language summaries for participants and patient advocacy organizations.

The study has been registered in the Japan Registry of Clinical Trials (registration number: jRCT1030250737; registration link: https://jrct.mhlw.go.jp/latest-detail/jRCT1030250737; February 17, 2026). The registration includes the details of the study objectives, design, and data management procedures. Any protocol amendments will be reflected in updates to the records of the Japan Registry of Clinical Trials.

Participation in the study may involve temporary discomfort or psychological burden. Completion of the self-administered questionnaires (approximately 110 minutes in total) may impose a time burden on participants. Although no directly identifiable personal information will be collected, the risk of data breaches or unauthorized access cannot be eliminated.

To mitigate these risks, survey items have been restricted to the minimum necessary to achieve the study objectives. All research procedures will comply with national and institutional information security guidelines. Only devices with up-to-date security software will be used; temporary cloud-stored data will be promptly deleted; and all data will be stored in encrypted form and accessed exclusively by authorized researchers.

Participants who experience psychological distress during or after the study may contact the survey company’s consultation service or the research team directly. Participation will be voluntary, and participants may withdraw at any time. Responses will be analyzed only if the survey is completed and formally submitted.

## 3. Discussion

This study establishes the TAMS registry as a foundational resource for the transdiagnostic evaluation of QOL and related psychosocial factors, psychiatric symptoms, sleep characteristics, and attitudes toward digital health technology across individuals with mental disorders and physical conditions as well as healthy participants. The TAMS registry represents a first step toward addressing the longstanding fragmentation of mental health research by enabling the concurrent assessment of these domains within a unified framework. By adopting a registry design aligned with the FAIR principles, this infrastructure is intended to support data sharing, secondary analyses, and cumulative knowledge generation beyond individual studies.

More broadly, the significance of the TAMS registry lies in its potential to reshape how mental health outcomes are studied and interpreted. Prior research has frequently examined psychiatric symptoms, sleep characteristics, and psychosocial factors in isolation, limiting the reconstruction of multidimensional, patient-level profiles and the investigation of cross-domain relationships. By providing a unified framework across diagnostic groups, the registry enables the exploration of shared and disorder-specific patterns of psychosocial factors and sleep characteristics, thereby supporting transdiagnostic profiling and hypothesis generation rather than prespecified causal inference.

The inclusion of multiple diagnostic groups within a single registry further advances this objective by enabling direct comparisons across patients with mental disorders and physical conditions as well as healthy participants, using a common measurement framework. This design facilitates the identification of dimensions that cut across diagnostic categories while preserving the capacity to examine disorder-specific features. In this respect, the TAMS registry enables future stratified analyses, data-driven subtyping, and comparative research. Importantly, the alignment of the registry with the FAIR principles constitutes a methodological contribution in its own right. Despite the growing number of PROs registries, the explicit implementation of the FAIR principles in the design stage remains limited. By systematizing data structures, metadata, and documentation to anticipate reuse, the TAMS registry lowers barriers to data integration and secondary use, promoting transparency, reproducibility, and international collaboration.

Beyond the inclusion of multiple diagnostic groups and FAIR alignment, the breadth of the instrument set reflects a deliberate design feature balanced against the trade-off of respondent burden. Cross-domain analyses spanning QOL, psychiatric symptoms, sleep characteristics, and attitudes toward digital health technology are difficult to reconstruct from narrower, domain-specific assessment strategies alone, which has been the dominant approach in prior research and a key gap this registry was designed to address. To balance this comprehensiveness against participant burden, the protocol deliberately employs (i) brief or screening-grade instruments where psychometrically defensible (e.g., K6, GAD-7, PHQ-9, DQ5-J, EQ-5D-5L); (ii) selective administration of relevant subscales rather than full inventories where appropriate (e.g., only 2 subscales of the MCQ-30, only the attention-control subscale of the EC, only the coping-strategies subscale of the CAS-1R, and the short form of the AQ); and (iii) operational features that mitigate fatigue during administration (auto-save on page transition, pause-and-resume within a 24-hour window, and a quality-check pledge item; see Section 2.8). We nevertheless acknowledge that respondent burden remains substantial, and the present design should be understood as a deliberate trade-off between analytic breadth and participant burden.

Operationally, the cross-sectional design means nationwide online panel data are collected by a survey company with participant identification assured; however, the analytic dataset contains no directly identifiable personal information. Following publication of the primary results, the data are planned to be released as open data under a CC BY 4.0 license and made available for direct download from a DOI-minting repository. This data-sharing strategy is expected to promote broad secondary use, including reanalysis and comparative research, while maintaining ethical safeguards and transparency, contributing to research reproducibility and the accumulation of international evidence in mental health research.

Some limitations should be noted. First, although the use of a nationwide online panel facilitated rapid enrollment, it could have introduced selection bias and limited broad generalizability [93]. The online panel sample may differ systematically from general clinical populations in terms of health consciousness, digital literacy, and willingness to participate in research [94,95]. Conversely, reliance on pre-registered disease-specific panels may underrepresent individuals with more severe illnesses or lower treatment engagement, potentially biasing the estimates toward milder presentations. Prior evidence suggests that individuals with mental disorders tend to be slightly underrepresented in general population-based surveys [96], and the direction of this selection bias should be considered when interpreting findings.

Second, diagnostic classification relied on participant-reported physician diagnosis, confirmed by a screening item at survey entry; it was not independently verified through medical records or structured diagnostic interviews for any diagnostic group, including the psychiatric disorder and diabetes groups. Research comparing self-reported diagnoses with symptom-based diagnostic methods in large online cohort studies has demonstrated only moderate agreement, with a substantial proportion of individuals with self-reported diagnoses not meeting symptom-based criteria, and vice versa [97]. Diagnostic misclassification of this form is likely to attenuate true between-group differences, potentially leading to an underestimation of associations between diagnostic group membership and the outcomes of interest. For psychiatric disorder groups, analyses restricted to participants whose self-reported diagnosis is corroborated by scores meeting established clinical cutoffs on the corresponding symptom measures may provide supplementary information; however, such analyses would necessarily exclude participants who are in remission at the time of assessment (such as individuals with a valid lifetime diagnosis whose current symptom scores fall below clinical thresholds) and would represent a systematically different subsample from the primary analyses [97]. For the diabetes group, symptom-based corroboration is not feasible as no corresponding symptom severity measures were collected. As a complementary sensitivity analysis, where suitable external estimates of the sensitivity and specificity of participant-reported history of physician diagnosis are available for a given disorder, quantitative bias analysis methods may be explored to assess the potential impact of diagnostic misclassification on selected prevalence or between-group estimates. For prevalence-type quantities, this may include classical correction approaches such as the Rogan–Gladen estimator [98], whereas broader probabilistic bias analysis frameworks may also be considered [99]. However, because valid external sensitivity and specificity parameters are not uniformly available across all disorders included in the registry, this approach is not prespecified as a systematic analysis across all diagnostic strata.

Third, a more fundamental limitation of the cross-sectional design is the inability to distinguish state from trait (e.g., whether poor sleep is a cause or a consequence of depression) and the inability to infer causal directionality in mediation models. All mediation analyses and structural equation modeling (SEM) models employed across the registry should be interpreted with caution, as the relations identified reflect statistical associations only and do not support causal inference. Indeed, cross-sectional mediation analyses yield biased estimates of longitudinal indirect effects [100]. The moderated mediation analyses in Sub-study 1d are subject to the same constraint and can only characterize conditional association patterns, not causal mediation. Therefore, the findings should be interpreted as hypothesis-generating evidence to be examined in future longitudinal designs.

Finally, although several measures were implemented to minimize careless responding before data collection, including a quality-check pledge item and built-in logic and consistency checks, the identification of inattentive responding in clinical populations presents methodological challenges. Commonly used detection indices, such as longstring analysis, Mahalanobis distance, and intra-individual response variability, may be confounded with respondents’ characteristics and genuine response tendencies, making it difficult to determine whether flagged responses reflect genuine inattention or valid patterns of responding [92,101]. Accordingly, the potential presence of residual inattentive responding cannot be ruled out as a source of measurement error in the present data.

Looking ahead, the TAMS registry may provide a foundation for future longitudinal extensions. Subject to funding, ethics approval, and the operational feasibility of panel re-contact through the survey provider, a follow-up wave could be considered using an abbreviated core-PROs battery to reduce respondent burden while preserving the main cross-domain constructs. In addition, FAIR-aligned release of the baseline dataset may facilitate harmonization or comparative use alongside independent longitudinal datasets. Such extensions could help examine temporal ordering more directly, evaluate the stability of transdiagnostic profiles over time, and characterize longitudinal changes in attitudes toward digital health technology.

In summary, the TAMS registry, a PROs registry that integrates a comprehensive set of indicators within a single standardized framework is expected to elucidate both common and disorder-specific structures as well as provide a foundation for advancing psychiatric research and patient-centered care. At the theoretical level, the registry is positioned to support the empirical examination of transdiagnostic dimensional structures [19,20], contributing to the development of more integrated psychopathology models that transcend traditional categorical nosology. At the practical level, registry-derived transdiagnostic profiles may inform measurement-based approaches to clinical assessment [7,8,9,10], support evidence-based health policy and resource allocation, and guide the design of digital technologies in the mental health domain by situating attitudes and ethical concerns within the broader context of clinical outcomes [31,32,33].

